3. ECG
4. Blood pressure
5. Haematology
6. Biochemistry
7. Urinalysis
8. Hormones
9. BSA
10. PGA
11. PASI and VAS (if applicable)
12. Sampling for serum/plasma biomarkers
13. Concomitant medication
14. Local tolerability
15. Adverse events
16. PK sample (through value)
17. IVRS dispensing call

Thereafter trial product administration will occur.

### **Samplings and recordings occurring after trial product administration:**

1. ECG will be recorded at 2 and 4 hours after each drug administration.
2. Blood pressure will be measured at 2 and 4 hours after each drug administration.
3. After each drug administration subjects will be closely monitored during their 4-hour-stay.
4. Drug accountability will be performed via **IVRS**.

Day 15: Sampling for molecular biomarkers, lesional skin biopsies (1x6 mm to be split in half). The skin biopsy procedure is optional.

Day 43: Sampling for antibodies.

Subjects are allowed to leave the site 4 hours after drug administration when all samples have been collected and all assessments have been recorded.

#### **Day 44**

Subjects must return to site for a 24-hour PK sample after the last drug administration.

#### **Day 57 to Day 148 (± 3 days)**

Subjects will come for regular visits at Day 57, 71, 99, 127 and 148. From Day 57 and onwards a deviation of ± 3 days from the scheduled day will be allowed. The following data and samples will be recorded and collected at each of those visits:

1. Vital signs
2. Haematology
3. Biochemistry
4. Urinalysis
5. Hormones
6. Sampling for serum/plasma biomarkers
7. PK samples
8. Concomitant medication
9. Local tolerability
10. Adverse events

Procedures which are not performed at every visit are listed below together with the time point at which they should be performed:

Day 57 (± 3 days): Lipids, ECG, BSA, PGA, PASI and VAS (if applicable), and quality of life questionnaire. At trial Day 57 all subjects must have been **fasting since midnight the same day** (only water will be allowed from midnight until collection of blood samples).

Day 99 (± 3 days): BSA, PGA, PASI and VAS (if applicable), and sampling for antibodies. Collection of lesional skin biopsies (1x6 mm to be split in half) is optional.

Day 148 (± 3 days): Body measurements (weight only), physical examination, ECG, BSA, PGA, PASI and VAS (if applicable), sampling for antibodies, and quality of life questionnaire.

#### **8.1.4 Recordings**

Exact dosing times, exact sampling time points for PK samples, and other serum, blood or plasma samples will be recorded directly in the electronic case record form (eCRF). Furthermore, PASI, PGA, BSA and VAS (if applicable) scores will be assessed/calculated and recorded in the eCRF.

Screening failures will be defined as those subjects who do not fulfil the eligibility criteria. These subjects are not eligible for the trial. At a minimum the reason for exclusion must be recorded in the screening failure form. Retesting of hepatic function (ALT and AST) is permitted within one week if first test is elevated. Screening visits are permitted to be rescheduled within one week, without taking new samples.

The screening failure form will be entered into the eCRF.

An overall interpretation of the ECG will be recorded in the eCRF and the recordings will be kept at site. Laboratory results will be entered in the Oracle Clinic data base.

Subjects may be identified through IVRS in the MD dose-escalation phase and MD expansion phase.

Subjects enrolled in the trial should be provided with a card stating that he/she is in a trial, contact address and telephone number.

In case a subject is being prematurely withdrawn from the trial the Investigator will ensure that the procedures for the last visit is undertaken, if possible. The primary reason (adverse event, non-compliance with protocol or other) for discontinuation must be specified in the eCRF. Even if the subject is not able to attend, the end of trial form must be completed and drug accountability must be performed.

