#### MD expansion phase

- The primary endpoint for efficacy is PASI (PASI75).

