**Table 5–1 Dose levels for the SD and MD dose-escalation phases and proposed initiation times.**

| Time when the different dose levels will be started (weeks) | SD, mg/kg                     | MD, mg/kg
(accumulated doses after four administrations) |
|-------------------------------------------------------------|-------------------------------|-------------------------------------------------------------|
| FPFV (W 0) to LPLV (W 55)                                   | Maximum dose level
3 mg/kg | Maximum dose level
2 mg/kg                               |
| W* 0                                                        | Level 1: 0.01                 |                                                             |
| W 5                                                         | Level 2: 0.05                 |                                                             |
| W 10                                                        | Level 3: 0.20                 |                                                             |
| W 15                                                        | Level 4: 0.6                  | Level 1: 0.05 (0.2)                                         |
| W 20                                                        | Level 5: 1.5                  |                                                             |
| W 25                                                        | Level 6: 3.0                  | Level 2: 0.20 (0.8)                                         |
| W 35                                                        |                               | Level 3: 0.5 (2.0)                                          |
| W 45                                                        |                               | Level 4: 1.0 (4.0)                                          |
| W 55                                                        |                               | Level 5: 2.0 (8.0)                                          |
| LPLV: W 77                                                  |                               |                                                             |

\* Related to the dosing of the first subject in the trial, and not to trial Week of each individual subject.

Dosing will occur every second week during the MD phases (dose-escalation and expansion phase), for a total of four doses. All subjects will be followed for 16 weeks after last dose and with a

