#### **6.4 Withdrawal criteria**

The subject may withdraw at will at any time.

The subject may be withdrawn from the trial at the discretion of the Investigator or the sponsor due to safety concerns, or if judged non-compliant with trial procedures.

A subject must be withdrawn if the following applies:

1. Non-compliance with protocol procedures
2. Drug limiting toxicity (DLT) or other serious or significant adverse event that warrants discontinuation in the opinion of the investigator
3. Sponsor closure of the trial
4. Withdrawal of informed consent

For the MD dose-escalation phase and the MD expansion phase an **IVRS call** must be performed if the subject is withdrawn.

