### **10.2 Breaking of blinded codes**

The code for a particular subject may be broken in a medical emergency, if knowing the identity of the treatment allocation would influence the treatment of the subject. Whenever a code is broken, the person breaking the code must record the time, date and reason as well as his/her initials in the source documents. The subject should be withdrawn from the trial if the code is broken.

If the trial site needs to break the code, the sponsor should, if possible, be contacted prior to breaking the code. In all cases, the monitor must be notified within 24 hours after the code has been broken.

The treatment will be accessible for Investigator, Novo Nordisk Affiliate and International Product Safety, using IVRS for code breaking. The contingency plan for code breaking is using ClinPhone Support, available 24/7.

The central laboratory will not be provided with treatment reports. However, a copy of the treatment reports will be forwarded to the person responsible for bioanalysis of 109-0012 in DMPK & Bioanalysis, Novo Nordisk A/S, in order to facilitate the availability of intermediate PK results to be used for the safety evaluation during the trial. A copy of the the treatment reports will also be forwarded to the person responsible for PK/PD analysis in Biomodelling, Novo Nordisk A/S, in order to begin exploratory model development to assess the pharmacokinetic/pharmacodynamic properties of 109-0012.

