## 16 Evaluability of subjects for analysis

All subjects exposed to trial drug will be included in the safety analysis set used for analysis of safety data. All randomised and exposed subjects will be included in the intention to treat (ITT) analysis set used for the efficacy analysis. The per protocol (PP) analysis set will be comprised of subjects from the ITT analysis set who have fulfilled all inclusion and no exclusion criteria at entry, as well as no withdrawal criteria during trial. The PP analysis of the efficacy data will be viewed as a supportive analysis. The PK/PD analysis set used for the analysis of the PK/PD data will include subjects from the ITT analysis set who have not committed any protocol violations judged to interfere with the pharmacokinetics/pharmacodynamics of 109-0012.

The decision to exclude any subject or observation from statistical analysis is the joint responsibility of the International Trial Manager, Sponsor's Medical Expert and the Statistician. The subjects or observations to be excluded and the reason for their exclusion will be documented and signed by all relevant parties at a review of data prior to database release.

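### An MD expansion subject withdrawn before Day 57 stays in the ITT set, but the protocol does not ask for the Day 57 PASI that defines the primary endpoint

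*Protocol*

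**What the plan says.** - **Early exit.** Section 8.1.4 provides that, when a subject is "prematurely withdrawn from the trial the Investigator will ensure that the procedures for the last visit is undertaken", this is to be done where feasible. In the MD expansion phase the last visit is Day 148 (8.1.3). Its list includes "physical examination, ECG, BSA, PGA, PASI and VAS (if applicable), sampling for antibodies, and quality of life questionnaire", on top of the vital signs, laboratory and PK samples taken at every late visit.
- **When withdrawal is imposed.** Section 6.4 makes withdrawal mandatory for, among other reasons, "Non-compliance with protocol procedures". Section 10.2 adds: "The subject should be withdrawn from the trial if the code is broken".
- **Primary endpoint.** PASI75 is primary for the expansion phase (4.2). Sections 17.1 and 17.2.2 fix it at two weeks after the fourth dose, Day 57, against the pre-dose baseline.
- **Analysis set.** Section 16: "All randomised and exposed subjects will be included in the intention to treat (ITT) analysis set used for the efficacy analysis".
- **Replacement.** Sections 6.5 and 10.1 have subjects who leave the MD phases before completing Day 57 replaced.
- **Follow-up.** In 5.3, below Table 5–1: "All subjects will be followed for 16 weeks after last dose", with the reason that the drug should by then have been sufficiently cleared at a half-life of about 15–20 days. Section 12.3 keeps serious events, and severe or possibly/probably related non-serious events, under follow-up until recovery, with exceptions such as chronic conditions.

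**The concern.** The protocol does not separate stopping trial product from leaving the trial. A subject withdrawn on, say, Day 30 has the last-visit procedures if they can be arranged, and no later visit is provided for. That subject counts in the efficacy analysis without a scheduled measurement at the primary time point. Two of the triggers, non-compliance and a broken code, do not in themselves prevent a later PASI, so part of the loss would come from the plan rather than from subjects declining to attend.

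An SAP can say how a missing Day 57 value is classified. It cannot schedule the visit that would have supplied it. Subjects withdrawn for toxicity in a first-human-dose trial are also those whose later PK, laboratory and antibody samples are most informative, and no such samples are provided for after exit.

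**Working it through.** **1. Passages side by side.** For withdrawal before Day 57 in the expansion phase:

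| Question | Where | Answer |
|---|---|---|
| Is the subject in the ITT set? | 16 | Yes, once randomised and exposed |
| When is PASI75 determined? | 17.1, 17.2.2 | Day 57 |
| What is collected on withdrawal? | 8.1.4, 8.1.3 | Day 148 list, where feasible |
| Is a return at Day 57 requested? | nowhere | No |
| Is 16-week follow-up due? | 5.3 | Yes, for all subjects |
| Are PK, laboratory or antibody visits provided for after exit? | nowhere | No |
| Does AE follow-up continue? | 12.3 | Yes, for serious, severe or related events |

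Doses fall on Days 1, 15, 29 and 43. A subject who exits before Day 43 has had at most three of four doses, so an exit PASI is not the measurement defined in 17.2.2. A subject withdrawn after Day 57 already has the primary assessment and is not affected on that point.

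**2. Drug remaining.** Assuming first-order decay of a single dose, the fraction left is 2^(−t/half-life).
- After 14 days: 2^(−14/15) = 52% and 2^(−14/20) = 62%.
- After 16 weeks (112 days): 2^(−112/15) = 0.6% and 2^(−112/20) = 2%.

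**3. The plan's own power.** Inputs from 17.1: 60% vs 10%, 26 + 13 subjects, two-sided Fisher's exact test, 5%. Power is the sum of Bin(x; 26, 0.60) × Bin(y; 13, 0.10) over all tables that reject. With 2.5% in the upper tail it is 83.8%, which matches the stated 83%. With the minimum-likelihood two-sided p-value it is 89.0%, which does not. The first convention is used below.

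**4. Rate of loss.** Section 6.1 plans 96 randomised and 83 completing: 13/96 = 13.5%. This covers all three phases and the whole of follow-up. The protocol gives no rate for loss before Day 57, so 13.5% is an assumption, shown within a range of 5–20%.

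**5. Effect if lost subjects count as non-responders (assumption).** A loss d in each arm multiplies both response rates by (1 − d). At 13.5% the rates are 0.60 × 0.8646 = 51.9% and 0.10 × 0.8646 = 8.6%. With replacement and everyone kept in ITT, the arms grow to 26/0.8646 ≈ 30 and 13/0.8646 ≈ 15.

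| Loss before Day 57 | Power, 26 + 13, no replacement | Power with replacement (randomised) |
|---|---|---|
| 5% | 79.8% | 83.4% (27 + 14) |
| 10% | 75.2% | 81.0% (29 + 14) |
| 13.5% | 71.5% | 79.6% (30 + 15) |
| 20% | 63.9% | 78.0% (32 + 16) |

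The replacement column assumes that replacements keep the 2:1 split. Section 6.5 requires the same treatment only in the dose-escalation phases.

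**The case against.** The strongest counter-argument is replacement. The total of 83 equals 24 + 20 + 39, and 6.1 labels it as completers, so the 39 are already net of loss and the replacement rule is tied to Day 57 itself. This stands as far as size is concerned: the with-replacement column is the one that fits the plan, and the cost in power is about 4 points at 13.5%, not 12. It does not remove the point, because the replaced subject remains in the ITT set without the primary outcome.

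Several stronger readings are tempting, but the documents do not support them.

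- A reader might infer that withdrawal ends all follow-up. Section 8.1.4 does not say so, 5.3 says that all subjects are followed, and 12.3 keeps the important adverse events under follow-up. What is missing is any provision for PK, laboratory and antibody visits after exit.
- A reader might compute power falling from 89.0% to 79.8%. That starts from a figure other than the protocol's 83% and ignores replacement. Under the same minimum-likelihood convention with 30 + 15, power is 84.0%.
- A reader might infer that loss will differ by arm, through adverse events on active and lack of effect on placebo. This could happen and would bias a 39-subject comparison, but the protocol offers no evidence for it, and lack of effect is not a listed withdrawal criterion in 6.4.
- A reader might fault the absence of a rule for missing PASI75. That can properly sit in the SAP, which is not at hand.

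**Conclusion.** The point holds, limited to withdrawal before Day 57. The protocol keeps such subjects in the primary analysis set, does not ask for their primary measurement, and in some cases imposes the withdrawal for reasons that leave a PASI feasible. Section 8.1.4 is also unreconciled with the follow-up statement in 5.3.

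The effect on power is modest if replacement works as written: 83.8% to about 79.6%, against 71.5% without replacement. Both figures rest on a borrowed 13.5% rate, equal proportional loss in the two arms and non-responder scoring, none of which the protocol states for this phase. The firmer reason to act is that an outcome never collected cannot be recovered by replacement or by the SAP. The change should be made, but the trial does not fail without it.

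**What to change.** In 8.1.4, state that MD expansion subjects withdrawn before Day 57 who have not withdrawn consent are asked to attend the already scheduled Day 57 assessment (PASI, PGA, VAS where applicable, DLQI) and the scheduled post-dose follow-up visits. Keep the last-visit procedures at exit for those who decline.

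Reconcile 8.1.4 with 5.3, 6.4, 6.5, 10.2 and 16, so that it is clear what a withdrawn subject is still asked to attend and how that fits with replacement and ITT membership. The rules on stopping treatment and on breaking the code are for the sponsor to settle.

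The cost is protocol and consent wording, plus a few visits already in the schedule for a handful of subjects. At the assumed 13.5%, about 6 subjects would be concerned (30 + 15 randomised less 39 completers).

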#### **8.1.5 Subject related information and assessments**

Demography: Information about date of birth (age), sex and ethnicity will be recorded.

Medical history: Subjects will be asked about previous diseases, specifically about malignancies, active herpes/herpes zoster/cold sores, tuberculosis, lymphoproliferative diseases, hepatitis, HIV, and infectious diseases requiring systemic treatment within the last 2 weeks, as well as squamous or basal cell carcinoma within the last year.

Concomitant illnesses: From trial Day 1 and onwards subjects will be asked about onset of new diseases, developing during the course of the trial. Specific tests to determine if the subject is infected by hepatitis B and C and/or tuberculosis will be performed during screening only.

Test for hepatitis B and C: A blood test to determine if the subject is positive for hepatitis B and/or C will be taken at screening.

Test for tuberculosis: A test to determine if the subject is positive for tuberculosis will be taken at screening.

Body measurements: The height and weight of the subject will be recorded and the body mass index (BMI) will be calculated as:

$$\text{BMI} = \text{weight (kg)} / [\text{height (m)}]^2$$

Pregnancy test (if applicable): Only women of non-childbearing potential and postmenopausal women (for at least 1 year) will be included. Otherwise FSH levels must be at least 40 mIU/mL, but if in doubt a regular urine pregnancy test will be performed.

## **8.2 Assessments for safety and tolerability**

Safety will be regularly evaluated during the trial. This is done by recording adverse events and toxicity to Anti-IL-20 (109-0012) 100 mg/vial. Adverse event severity is defined by NCI's CTCAE, version 3.

### **8.2.1 Adverse events**

Adverse events, including local irritation at injection site, will be checked regularly during the entire trial.

#### Local irritation at injection site:

If an injection site reaction is observed, it must be recorded as an adverse event, with a specific description of the type of event such as:

- Redness
- Oedema
- Itching
- Burning
- Numbness
- Pain
- Eczema

The time of onset, duration and the size of the area must also be reported.

The following parameters are regarded as secondary safety endpoints and will be evaluated throughout the trial:

- Vital signs (blood pressure, pulse, and body temperature)
- 12-lead ECG
- Laboratory safety parameters haematology, biochemistry, hormones lipids, and urinalysis
- Immunogenicity
- Physical examination

### **8.2.2 Vital signs**

Supine systolic and diastolic blood pressure as well as pulse should be measured after 5 minutes rest in supine position. Tympanic temperature should also be measured.

### **8.2.3 12-lead ECG**

A standard 12-lead ECG will be performed while the subjects are in supine position. The evaluation should be recorded in the eCRF and judged as one of the following at screening visit:

- Normal
- Abnormal, not clinically significant
- Abnormal, clinically significant

ECG evaluations will be performed centrally.

### **8.2.4 Laboratory safety parameters**

#### Biochemistry:

Adiponectin

Alkaline phosphatase (ALP)

Aspartate aminotransferase (AST)

Alanine aminotransferase (ALT)

Albumin

Calcium

Calcitonin

Chloride

CRP (C-reactive protein)

Creatinine

Creatinine kinase

Gamma glutamyltransferase

Glucose

Homocystein

Lactate dehydrogenase  
Magnesium  
Phosphate  
Potassium  
Sodium  
Total bilirubin  
Total protein  
Urea  
Uric acid

Haematology:

Basophils  
Eosinophils  
Erythrocytes  
Erythrocyte sedimentation rate (ESR)  
Haemoglobin  
Haematocrit  
Leucocytes  
Lymphocytes (differential counts)  
Monocytes  
Neutrophils  
Total erythrocyte and leukocyte count  
Thrombocytes

Urinalysis: pH, protein, glucose, blood, bilirubin.

Lipids (only for the MD dose-escalation and MD expansion phases): Cholesterol, low density lipoprotein (LDL) cholesterol, high density lipoprotein (HDL) cholesterol. Subjects must be fasting from midnight the same day of sample collection, only water is allowed.

Hormones: Thyroid stimulating hormone-P (TSH), IL-1 $\beta$ , IL-6, TNF- $\alpha$ , INF- $\gamma$  and follicle stimulating hormone (FSH) if applicable.

#### **8.2.4.1 Handling of blood and urine samples**

The analyses of haematology, biochemistry, hormones, lipids and urine samples will be performed at the local laboratory for the SD dose-escalation phase and at the central laboratory for the MD phases, according to their standard methods. The handling procedures of these samples will be performed according to the laboratory manual. Values outside standard ranges will be noted and the

Investigator must evaluate if the results are likely to be clinically significant or not. Clinically significant laboratory values qualify as adverse events and must be reported (see Section [12.2](#)). Laboratory results must be signed electronically by the Investigator within 24 hours after receipt. The analytical reports must be sent to Novo Nordisk.

### **8.2.5 Immunogenicity**

Immunogenicity (antibodies to 109-0012) samples will be analysed at Novo Nordisk using assays validated to detect the presence of antibodies against 109-0012 in human serum. Analysis for antibodies during the SD dose-escalation phase will only be performed if there are any safety concerns which are believed to be correlated to antibody production.

#### **8.2.5.1 Handling of immunogenicity samples**

After blood sampling (in normal serum sampling tubes) samples should be kept at room temperature for 1 hour before centrifugation to generate at least 0.5 mL serum, where possible. Serum should be transferred to cryotubes and stored at -20 °C. The tubes should be labelled with:

- Study ID
- Subject ID
- Nominal sampling time point
- Date of sampling
- Visit No.

The samples should be stored and shipped at -20 to -35°C.

